### NGF Injection

Repeated intramuscular injection of NGF induces progressive, persistent muscle pain that is mechanistically, functionally, and clinically relevant. Importantly, NGF induces a gradual onset of pain without tissue injury [91], mimicking key features of persistent musculoskeletal pain, including movement-evoked pain, spreading hyperalgesia, and functional limitation [92,93], which resolve spontaneously around 25 days after injections have ceased [39,94]. These characteristics make the NGF model a safe and clinically relevant approach to investigate the cortical mechanisms underlying pain-related motor behavior and its individual variability, as it replicates the time course, movement-evoked nature, and sensitization processes characteristic of persistent musculoskeletal pain.

After cleaning the skin with alcohol, a solution of recombinant human NGF (Active GMP Recombinant Human NGF Protein from Creative BioMart Inc) will be administered as a bolus injection of 5 μg, dissolved in 0.2 mL of sterile water, into the muscle belly of the right ECRB muscle at the end of visits on days 0 and day +2. The injection will be administered using a 1-mL syringe with a 27-gauge, 1-inch needle. The site of injection will be located 1 cm lateral to a point that is 5 cm distal to the lateral epicondyle, along a line connecting the lateral epicondyle to the midline of the wrist [39,95]. The participant’s upper limb will be supported on a table, with the elbow flexed to 90° and the forearm in pronation to ensure proper positioning and accessibility to the target area. A permanent marker will be used to circle the injection site to maintain consistent injection placement in the ECRB muscle throughout the visits. In order to ensure optimal effectiveness of the hyperalgesia, we will keep the NGF at a temperature of −80 °C until a few minutes before the injection [96].

### Questionnaires

All questionnaires will be computerized and sent via Qualtrics Survey Software (version XM; Qualtrics, LLC). Patient-Rated Tennis Elbow Evaluation (PRTEE) is a 15-item questionnaire designed to measure forearm pain and disability in patients with lateral epicondylitis, also known as tennis elbow [97-99]. It consists of 2 subscales: a 5-item pain subscale and a 10-item function subscale, with each item rated on a scale of 0-10. The pain subscale is scored out of 50, and the functional subscale is divided by 2 to bring it down to a score out of 50 for a total score out of 100. The PRTEE has demonstrated high test-retest reliability (intraclass correlation coefficient [ICC]=0.96), internal consistency (Cronbach α=0.96) [99], and shows good construct validity against other measures such as the Disabilities of the Arm, Shoulder and Hand (*r*=0.81) [100]. The PRTEE is considered a reliable and valid tool for assessing pain and functional disability in patients with lateral elbow tendinopathy.

Tampa Scale for Kinesiophobia (TSK) is a widely used self-report questionnaire using a 4-point Likert scale, designed to assess fear of movement [101]. The objective of the TSK is to quantify kinesiophobia, defined as an irrational and debilitating fear of physical movement resulting from a feeling of vulnerability to painful injury or reinjury [102]. The TSK has demonstrated good to excellent test-retest reliability (ICC=0.77-0.99) and good internal consistency (Cronbach α=0.68-0.91) across various versions [103,104]. We have selected the TSK-13 (13 items), which presents good construct validity and strong psychometric properties, for a reduced completion time [103,105]. Participants will be asked to rate their agreement with the item statements from “*strongly disagree*” to “*strongly agree*,” with total scores ranging from 13 to 52, where higher scores indicate greater kinesiophobia [106]. Because the questionnaire was initially designed for patients with musculoskeletal pain, the questionnaire’s instructions were adapted to align with our healthy participants, following the validated TSK-G version for the general population [107], as done in previous studies [108-110]. The revised instructions were as follows: “We are interested in the types of thoughts and feelings that you might have in response to pain. Please read each of the following statements and check the box that best represents your thoughts and feelings while experiencing muscle pain.”

Pain Beliefs Questionnaire (PBQ) is a self-report instrument designed to assess individuals’ beliefs about the causes and consequences of pain [111]. Initially developed as a 20-item questionnaire, it was later refined to a 12-item version comprising 2 subscales: the Organic Beliefs Scale (8 items) and the Psychological Beliefs Scale (4 items) [112]. The PBQ evaluates pain-related beliefs, particularly the perceived organic nature of pain and the role of psychological factors in pain perception. The questionnaire has demonstrated strong construct validity, with patients with chronic pain and healthy controls exhibiting significant differences in their endorsement of organic and psychological beliefs [111]. It also shows good internal consistency (Cronbach α=0.68-0.91) across different versions [113]. Respondents rate their agreement with each statement on a 6-point Likert scale from “*always*” to “*never*.” The PBQ has been effectively used in studies on chronic back pain and is applicable to both individuals experiencing pain and healthy controls [112]. Its ability to assess pain beliefs across diverse populations makes it a valuable tool for understanding pain perceptions and informing pain management strategies.

Coping Strategies Questionnaire–Revised (CSQ-R) is a 27-item self-report instrument designed to assess cognitive and behavioral strategies for coping with pain [114]. It evaluates 6 key domains: Distraction, Catastrophizing, Ignoring Pain Sensations, Distancing from Pain, Coping Self-Statements, and Praying. The CSQ-R demonstrates a robust factorial structure, high reliability, and strong validity across multiple studies. Its subscales show excellent internal consistency (Cronbach α=0.914-0.961) and good to excellent test-retest reliability (ICC=0.850-0.918). Construct validity is supported by significant correlations with measures of pain, disability, depression, and other coping inventories. Administered as a self-report measure, the CSQ-R requires respondents to rate the frequency of their use of each coping strategy on a Likert scale from 0 “*never*” to 6 “*always*.”

Likert Muscle Soreness Scale (LMSS) is a self-report tool designed to assess perceived muscle soreness, particularly in the context of delayed onset muscle soreness. Its primary objective is to quantify the severity of muscle soreness and its impact on functional tasks using a 7-point scale ranging from 0 (no pain) to 6 (severe pain limiting movement) [115]. It has demonstrated good construct validity, with significant correlations (*r*=0.65-0.941) to other pain measures, such as the visual analogue scale, and its reliability is sensitive to changes in soreness over time [116]. Administered as a self-report measure, participants rate their soreness based on predefined descriptors. The LMSS has been validated in various populations, including long-distance runners and soccer players, confirming its applicability across different athletic groups [115]. The LMSS will be tailored to best match the elbow pain we will induce with the NGF injection by adding the italicized words at the end of the instructions as follows: “Please tick the sentence below that best describes your level of muscle soreness over the past 12 hours *related to the injection*.” For the same reason, the last 4 items will be adapted for the elbow pain as follows: “A light muscle soreness when I move my elbow/wrist in a large amplitude or/and when I handle an object with force”, “A light muscle soreness, stiffness or weakness when I move my elbow/wrist or/and when I handle an object with finesse,” “A moderate muscle soreness, stiffness or weakness when I move my elbow/wrist or/and when I handle an object with finesse” and “A severe muscle soreness, stiffness or weakness that limits the ability to move my elbow/wrist or/and handle an object.”

McGill Pain Questionnaire–Short Form (MPQ-SF) is a widely used self-report instrument designed to assess the multidimensional nature of pain [117]. The MPQ-SF consists of 15 descriptors (11 sensory and 4 affective) each rated on a 0 “none” to 3 “severe” intensity scale. The MPQ-SF provides a concise yet comprehensive measure of both sensory and affective pain dimensions, making it suitable for clinical and research settings. The MPQ-SF has demonstrated strong psychometric properties across various chronic pain populations, with high internal consistency (Cronbach α=0.73-0.89) [118] and excellent test-retest reliability (ICC=0.96) [119]. Validity studies support its construct and concurrent validity, showing strong correlations with other pain measures and sensitivity to changes in pain intensity.

*Body diagram* in the McGill Pain Questionnaire is a widely used tool for assessing pain location and distribution. It provides a visual representation of a patient’s pain by allowing them to mark affected areas on anterior and posterior body schematics including 9 areas: trunk, head and neck, shoulder, arm, elbow, forearm, hand, thumb, and fingers. The test-retest for measuring pain distribution demonstrated a moderate to excellent reliability (ICC=0.58-0.94), but which shows a great variability of reliability to assess the localization of pain, according to the specific circumstances of the evaluation (κ=0.13-0.85) [120]. The administration of body diagrams is typically self-reported, with patients marking their pain on the diagram following standardized instructions.

### Sample Size

The trial is conservatively powered based on the use of separate multiple regression models to determine which mechanistic variables predict motor outcome at each time point. This calculation is based on 20 mechanistic variables: sensorimotor cortex excitability × 4 (map, SEPs, SICI, and ICF), sensorimotor integration × 1 (PAF-EEG), pain modulation × 2 (HPTs and PPTs), cognitive response × 4 (MSIT-easy-hard × 2 conditions), and physical activity or cognitive response × 6 (MPQ-SF, TSK-13, CSQ-R, PRTEE, LMSS, and PBQ), plus 3 a priori selected interactions and demographic variables × 3 (age, sex, and gender). We require 150 participants to achieve a power of 80% with a 5% significance level to detect a medium effect size and allowing for 10% loss to follow-up (based on our prior studies). The significance level was adjusted for multiple testing using a Bonferroni correction with an assumed correlation between predictors of 0.1. Using an alternative approach of 5‐10 participants per parameter, a sample of 150 could accommodate 15-30 parameters.

### Statistical Analysis

The analysis will be performed using growth curve modeling (GCMs) with the R software (R Core Team; R Foundation for Statistical Computing) for the 2 main outcomes [121]. Advantages to the use of GCM to examine our aim are as follows: (1) GCM enables consideration of the time-varying nature of both outcome (motor behavior) and the mechanistic (central nervous system) variables in response to pain; (2) GCM allows mechanistic variables to be simultaneously adjusted, permitting estimation of the unique contribution of each mechanism to motor behavior, as well as interaction between mechanisms; and (3) GCM can use unevenly spaced measurements and all available data, even in the presence of missing data at random. Thus, we will investigate whether mechanistic variables (and the interaction between them) at each time point, and the change between time points, predict motor behavior. To address individual variation in motor behavior, the model will use a 2-level nested structure. Level 1 will be the within-participant model and level 2 the between-participants model. The within-participant component allows each participant to have a unique motor behavior via random effects, and the between-participants component represents variation in motor behavior between individuals with similar mechanistic characteristics. The issue of controlling many covariates in statistical modeling will be addressed using modern adjustment techniques (eg, shrinkage estimation or exposure modeling) [122]. In addition, bootstrapping will be used to identify variables to be included in the final model [123]. Two models will be developed, 1 for kinematic movement variability and 1 for muscle synergies.

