For each visit, all 6 repetitions (3 clockwise turns and 3 counterclockwise turns) of the same movement will be averaged. The RMSD of concatenated individual hand trajectories relative to their own mean trajectory over the same visit will then be computed. This single scalar index of intravisit kinematic variability will then be entered into growth curve models to characterize longitudinal changes in movement dispersion across the 4 repeated visits independently of end point accuracy.

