EMG signals from the FCR, FCU, ECRB, and ECU muscles will be preprocessed using a customized MATLAB algorithm. The linear trend will be removed before filtering each signal with a fourth-order zero-lag band-pass Butterworth filter set between 20 Hz and 1000 Hz to remove motion artifacts at low frequencies and high-frequency noise. Full-wave rectification and smoothing through a fourth-order zero-lag low-pass Butterworth filter (cutoff frequency 5 Hz) will then yield EMG envelopes. Each muscle EMG envelope will subsequently be normalized by its peak activation observed across the whole visit, ensuring that synergy extraction reflects relative muscle coordination patterns independently of absolute activation magnitude. This normalization minimizes the influence of between-visit amplitude variability due to electrode placement, skin impedance, and amplifier gain, which are known to produce substantial day-to-day variability and can confound interpretation of activation amplitude [43-45]. This type of within-session peak normalization is commonly used when the focus is on coordination patterns and synergy structure, rather than on absolute activation levels [46,47]. Envelopes will then be cut using segmentation time stamps from kinematic data, and each of the 16 individual movements will be time-normalized to *t*=3000 samples. Individual movements will then be concatenated to represent the whole visit (6 turns) as a single data matrix. Spatial muscle synergies will be assessed each visit (*v*=4) from concatenated EMG envelopes by the nonnegative matrix factorization (NNMF) approach [48], as implemented in MATLAB (alternating least squares algorithm). The model will thus include for each participant and each visit the *m*=4 muscles (FCR, FCU, ECRB, and ECU) and all repeated (*r*=6) round trips corresponding to 16 pointing tasks (*k*=16). The NNMF approach can extract muscle synergies, *s* ranging from 1 to *m*–1=3. The spatial synergy (*U*, with *m* rows and *s* columns) and temporal coefficients (*C*, with *s* rows and *k × r × t* columns) will be identified from the preprocessed EMG matrix *M* (equation 1). This optimization will run 20 times to ensure the lowest possible reconstruction error (ε, with *m* rows and *k× r × t* columns; equation 1) since the NNMF method iterates from a random seed.

(1)
M=U⋅C+ε

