The reconstructed EMG matrix (equation 2) will be used to assess reconstruction quality using the variance accounted for (VAF) (equation 3). Unlike a coefficient of determination, the total sum of squares is not centered. VAF will be computed both globally and for each individual muscle (by setting the chosen muscle index and removing the summations over muscles in equation 3). A total of 20 VAF values will thus be associated with each participant [(*m* + 1) × *v*]. The minimal number of synergies required to reach satisfactory reconstruction quality will be optimized individually for each visit according to a threshold of 0.8 for each of the 5 associated VAF values (*m* individual muscle values plus global VAF).

(2)
$$\hat{M}=U\cdot C$$

(3)
$$VAF=1-\frac{\sum_{muscle=1}^{2}\sum_{time=1}^{t}{\left(M_{muscle,time}-{\hat{M}}_{muscle,time}\right)}^{2}}{\sum_{muscle=1}^{2}\sum_{time=1}^{t}M_{muscle,time}^{2}}$$

Synergy variability will involve only synergy activation variability since no motor adaptation should occur within 1 visit (no muscle synergy composition variability). The variability of activation coefficients will be quantified by the Pearson correlation coefficient (*r*), the maximum value of the normalized cross-correlation coefficient (*r*_max_), and the time shift between activation curves (lag_%_, expressed as a percentage of movement duration) between turns. All 3 variability metrics for each muscle synergy will be averaged across all pairwise combinations of the same 16 individual movements within a visit. *r, r*_max_, and lag_%_ values will finally be averaged over muscle synergies to reflect overall synergy activation variability. High muscle activation variability is reflected by low *r* and *r*_max_ values, as well as larger time shifts lag_%_. This approach is inspired by work based on the similarity of muscle synergy [49], although referring to activation similarity instead of activation variability. Metrics on intravisit muscle synergy activation variability (*r, r*_max_*,* lag_%_) will be compared between pain-free and pain-induced conditions regardless of muscle synergy composition between pain conditions.

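### The number of muscle synergies is re-chosen at every visit, so a visit change in the synergy metrics need not be a change in variability; the single synergy model also has three candidate outcomes and names none

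*Protocol article*

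**What the plan says.** In the Protocol article, the Statistical Analysis section applies growth curve models "for the 2 main outcomes" and adds: "Two models will be developed, 1 for kinematic movement variability and 1 for muscle synergies".

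For kinematics, the outcome is settled in the Kinematic Variability section: "This single scalar index of intravisit kinematic variability will then be entered into growth curve models".

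For synergies, the Muscle Synergies section sets out this sequence:

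- With four muscles, the factorization may return s = 1, 2 or 3 synergies.
- The number is picked per visit: "The minimal number of synergies required to reach satisfactory reconstruction quality will be optimized individually for each visit according to a threshold of 0.8". The threshold applies to five values, one global and one per muscle.
- Three metrics of activation variability follow: r, r_max and lag%. "All 3 variability metrics for each muscle synergy will be averaged across all pairwise combinations of the same 16 individual movements within a visit".
- Each metric's "values will finally be averaged over muscle synergies to reflect overall synergy activation variability".
- Pain-free and painful visits are then compared without regard to what the synergies are made of.

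No metric is named as the one that enters the model, and no composite is defined. The section reads low r, low r_max and larger shifts as high variability. It does not say in words that lag% is averaged as an absolute value.

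**The concern.** A repeated-measures outcome has to be the same quantity at every visit. Here the quantity is an average over a set of activation curves whose number is decided by a threshold, visit by visit. If a painful visit crosses the threshold and the baseline visit did not, the two visit values are averages over different sets of curves from different factorizations. The growth curve model would read the difference as a change in motor behavior.

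The Discussion expects more consistent synergy activation with pain. If adding a synergy lowers r, then a fall in the number of synergies under pain raises r and imitates that result, and a rise in the number hides it.

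The second matter is which number enters the synergy model. Motor variability, quantified by RMSD and muscle synergies, is the primary outcome in the Abstract. With three candidates and one model, the choice could be made after the results are seen.

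**Working it through.** **1. The plan's own count.** The article gives 20 VAF values per participant. With m = 4 muscles and v = 4 visits, (m + 1) × v = 5 × 4 = 20. This matches and confirms that the criteria are applied separately at each visit.

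**2. What a visit value is.** Six turns give 6 × 5 / 2 = 15 pairs per movement. Over 16 movements that is 15 × 16 = 240 pairwise values per synergy. The visit value is the mean of these, averaged over the s synergies. When s changes, the divisor changes, and so do the curves, because the factorization is redone.

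**3. Dependence on s with the signals unchanged.** The documents contain no EMG data, so the shapes below are assumed and the figures are illustrative. All simulations use four muscles; A and B use 16 movements × 6 turns. In each row the same data are factorized with s = 1, 2 and 3.

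| Simulation | mean r at s = 1 / 2 / 3 | mean absolute lag (%) at s = 1 / 2 / 3 | s chosen by the 0.8 rule |
|---|---|---|---|
| A (12 data sets) | 0.793 / 0.752 / 0.746 | 5.1 / 6.8 / 7.7 | 1 in ten, 2 in two |
| B, weak muscle coupling, timing SD 3% (6 data sets) | 0.890 / 0.903 / 0.848 | 1.55 / 2.33 / 2.79 | 2 in one, 3 in one, none qualified in four |
| B, medium coupling, timing SD 3% (6 data sets) | 0.899 / 0.905 / 0.843 | 1.53 / 2.38 / 2.60 | 2 in all six |
| B, strong coupling, timing SD 3% (6 data sets) | 0.894 / 0.903 / 0.670 | 1.60 / 2.48 / 3.56 | 1 in one, 2 in five |
| C, two true synergies, timing SD 2% | 0.91 / 0.70 / not run | rose from s = 1 to 2 | not recorded |
| C, three true synergies, timing SD 4% | 0.93 / 0.84 / not run | rose from s = 1 to 2 | not recorded |

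Change in r for one extra synergy:
- From 1 to 2: -0.041 in A; +0.013, +0.006 and +0.009 in B; -0.21 and -0.09 in C.
- From 2 to 3: -0.006 in A; -0.055, -0.062 and -0.233 in B.

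Absolute lag rose at every step. The recorded rises run from 0.21 (2.60 - 2.38, on unrounded values) to 1.7 percentage points (6.8 - 5.1).

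In A, and in B with weak or strong coupling, the rule gave different numbers to data sets generated with the same true variability.

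**4. Comparison with a real change.** In B with s held at 2, timing SDs of 1 / 3 / 6% give r of 0.939 / 0.903 / 0.806 and absolute lag of 0.88 / 2.46 / 5.08%. Tripling the true SD from 1% to 3% therefore lowers r by 0.939 - 0.903 = 0.036. Going from s = 2 to s = 3 on identical data (medium coupling) lowers it by 0.905 - 0.843 = 0.062.

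**5. The choice of metric matters.** In A, raising timing SD through 3 / 8 / 16% moves r through 0.92 / 0.76 / 0.41, but r_max only through 0.989 / 0.983 / 0.965. If the three metrics were independent and each tested at 0.05, the chance of at least one false positive would be 1 - 0.95³ = 14.3%. They all respond to the same variability and are correlated, so the true figure would be lower.

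**6. Why lag% should be defined.** For independent normal timing offsets, the mean absolute pairwise lag is 2 × SD / √π. SDs of 2, 4 and 8 give 2.26, 4.51 and 9.03, so the absolute form follows the spread. A signed mean has expectation zero at any spread.

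**The case against.** **The size depends on assumed shapes.** This stands. In B, r hardly moved between one and two synergies, and it moved slightly upward. A jump from 1 to 3 synergies gives a larger contrast in A, but the rule never chose 3 there, so that contrast should not be quoted as the expected effect. What remains is that absolute lag rose at every step and that r moved materially in several settings.

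**Comparing visits regardless of composition is a declared choice.** It is. The reason given, that no motor adaptation should occur within one visit, supports averaging within a visit. It does not make averages over different numbers of synergies comparable between visits.

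**No passage shows that pain changes the number of synergies.** Correct. The documents do not say how often it will change. They do set a rule that allows it.

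**A separate analysis plan may name the outcome.** Possible, and this tempers the second part. The Introduction does say that the article outlines the statistical analysis plan, and kinematics is given a single scalar. The per-visit rule is stated text, not an omission. The plan also commits to comparing all three metrics between pain conditions, which limits silent selection.

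**Stronger readings the documents do not support.**
- A reader might infer that lags are averaged with their sign and cancel. The text never says they are signed, and equating larger shifts with higher variability implies a magnitude. Only a clarification is due.
- A reader might infer that the three metrics are forced into one model. A composite or a multivariate model is not excluded.
- A reader might hold that averaging raw r without Fisher's transformation invalidates the model. No error distribution is specified, the Primary Outcomes overview allows reported adjustments for statistical assumptions, and no calculation here shows harm.

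**Conclusion.** The point holds in two parts, and the plan should be changed.

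First, choosing s per visit and averaging over s makes the synergy outcome depend on a threshold decision as well as on variability. That follows from the stated procedure. In the simulations, one extra synergy usually lowered r and always raised absolute lag, in some settings by more than a true tripling of timing SD from 1% to 3% did to r. These sizes rest on assumed EMG shapes. The frequency of changes in s between real visits is unknown, so the bias in this study cannot be given as a number.

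Second, the single synergy model lacks a named outcome among three metrics that respond very differently to the same change. The documents do not show that a selective choice is intended.

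The kinematic model is unaffected.

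**What to change.** - **Hold s constant within a participant.** Use one number at all four visits, for example the largest that any of that participant's visits needs to reach 0.8. Report the per-visit minimum as a description.
- **Add a sensitivity analysis with one common s for all participants.** A within-participant rule still lets s differ between people, and level 2 of the model compares people. It also lets a later painful visit determine the number used at baseline.
- **Name the outcome of the synergy model.** Mean pairwise r is one candidate, with r_max and lag% supportive. A composite defined in advance would also serve.
- **State that lag% is averaged as an absolute value.**

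Cost: plan wording and a rerun of the offline factorization, with no new measurements. Some visits will carry one more synergy than their minimum. By April 2026, 26 of 150 participants were enrolled, so the change can be made well before analysis.
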